## Abstract

**Introduction:**

Chronic pain (CP) is one of the most frequently presenting conditions in health care and many patients with CP report mental fatigue and a decline in cognitive functioning. However, the underlying mechanisms are still unknown.

**Methods and analysis:**

This study protocol describes a cross-sectional study aimed at investigating the presence of self-rated mental fatigue, objectively measured cognitive fatigability and executive functions and their relation to other cognitive functions, inflammatory biomarkers and brain connectivity in patients with CP. We will control for pain-related factors such as pain intensity and secondary factors such as sleep disturbances and psychological well-being. Two hundred patients 18–50 years with CP will be recruited for a neuropsychological investigation at two outpatient study centres in Sweden. The patients are compared with 36 healthy controls. Of these, 36 patients and 36 controls will undergo blood sampling for inflammatory markers, and of these, 24 female patients and 22 female controls, between 18 and 45 years, will undergo an functional MRI investigation. Primary outcomes are cognitive fatigability, executive inhibition, imaging and inflammatory markers. Secondary outcomes include self-rated fatigue, verbal fluency and working memory. The study provides an approach to study fatigue and cognitive functions in CP with objective measurements and may demonstrate new models of fatigue and cognition in CP.

**Ethics and dissemination:**

The study has been approved by the Swedish Ethics Review Board (Dnr 2018/424-31; 2018/1235–32; 2018/2395–32; 2019–66148; 2022-02838-02). All patients gave written informed consent to participate in the study. The study findings will be disseminated through publications in journals within the fields of pain, neuropsychology and rehabilitation. Results will be spread at relevant national and international conferences, meetings and expert forums. The results will be shared with user organisations and their members as well as relevant policymakers.

**Trial registration number:**

NCT05452915.

Strengths and limitations of this studyA large cross-sectional multicentre study including 200 patients and 36 controls.Studying fatigue in chronic pain with objective neuropsychological measurements as well as biomarkers and brain imaging is an innovative approach to finding underlying pathophysiological mechanisms in this condition.The patients are consecutive clinical patients currently being evaluated for pain rehabilitation, which means that the results from the study are clinically generalisable.A study limitation is the small size of the control group; however, the size of the control group is adapted for comparison of the results from the functional MRI examination and blood sampling.

## Introduction

Pain is one of the most frequently presenting conditions in healthcare. When pain has been present for 3 months, it is classified as chronic. In chronic pain (CP), the central nervous system (CNS) is affected by an imbalance in the ascendent and descendent tracts. This facilitates the pain and impedes pain inhibition. This, in turn, leads to plastic changes in the CNS, which are shown as increased sensitivity to pain and other stimuli, depression and fatigue.^1–3^

Fatigue is a common report across CP conditions, not least in widespread pain,^4–9^ and it is often reported to be one of the most burdensome symptoms.^10^ Fatigue, however, is difficult to investigate because it is subjective in nature and the definition of the concept is indistinct.^11^ Fatigue is usually measured by questionnaires, but when using questionnaires, the results often interfere with other psychological conditions, for example, depression,^12^ sleep disturbances^13^ or pain.^14^ As depression and sleep disorders are common in patients with CP, it is difficult to determine whether the fatigue seen in these patients is primarily related to pain or whether it is secondary to depression,^15^ which incites a general attitude that fatigue among patients with CP is due to sleep disorders and depression.^16^ Still, fatigue can, but need not, be linked to impaired cognitive functioning.^17^ Cognitive aspects of fatigue, cognitive fatigue, is a state where a cognitively demanding task gives rise to a mental/subjective experience of fatigue and has often been used synonymously with mental fatigue.^18^ However, it is still a subjective experience. Some cognitive aspects of fatigue can also be measured on a functional level as cognitive fatigability, defined as performance decline on attention-demanding tasks.^19–21^

It is well established from studies with self-reported data and cognitive tests that patients with CP are severely bothered by cognitive impairment,^22–24^ not least patients with generalised pain.^25^ Also, there are several studies showing an association between pain and deficits in attention, memory, processing speed and executive function.^22 26^ It is important to separate self-reported symptoms from functional disabilities on objective tests since, as noted above, self-reports can be influenced by psychological well-being.^27^

Impaired cognitive ability in CP has been explained either by ‘limited resources’ that is, that the pain competes for limited attentional resources in the brain,^25 28^ or by neuroplastic changes, where impaired cognitive ability in patients with CP is supposed to be caused by neurodegenerative processes. In CP, the CNS is affected by an imbalance in the brain’s pathway system, which leads to plastic changes in the brain.^1^ In particular, pain activates areas of the brain that are important for attentional functions, which may explain why many patients with CP experience attention deficits.^22^

In patients with acquired brain injuries and other neurological conditions, self-rated fatigue has been associated with impaired attention^29^ and slower processing speed.^30^ Fatigability in cognitively demanding tasks has been shown in patients with mild traumatic brain injury,^31^ multiple sclerosis^32^ and hormonal conditions,^33 34^ thus constituting an objective measure of cognitive fatigue. In acquired brain injuries and other neurological conditions, cognitive fatigue has been associated with dysfunctions in the corticostriatal networks in the basal ganglia.^35–38^ The relation between fatigue and attention deficits in CP has not yet been pinpointed in the literature, and cognitive fatigability has, to our knowledge, not been studied in patients with CP. It cannot be ruled out that fatigue in CP and neurological conditions might share underlying mechanisms, and that objectively measured cognitive fatigability could be an objective marker of cognitive fatigue also in CP.

As fatigue is an indistinctive report with multifactorial origin, the importance of a standardised taxonomy has been emphasised to clarify and improve the assessment and reporting of fatigue.^11^ Correlations between depression and self-rated fatigue are seen in several studies regardless of the underlying medical condition.^12 39 40^ Finding methods to capture fatigue without the result being affected by depression are important to disentangle other possible underlying causes of fatigue and thereby enable effective treatment. In previous studies on patients with brain injuries, cognitive fatigability has not been affected by depression.^41 42^ By combining self-rating measures and fatigue measures not related to depression but rather with functional networks in the brain^31^ or with results on cognitive tests,^41^ a clearer picture of possible underlying causes of fatigue can be obtained and in the long run also what treatment should be recommended.

Functional MRI (fMRI) may reflect increased or decreased neuronal activity in the brain as changes in neuronal activity are linked to changes in regional blood flow and blood oxygen level dependent (BOLD). With different fMRI techniques, it is possible to study whether discrete cerebral dysfunctions can be linked to self-perceived fatigue and cognitive fatigue/fatigability on a group level. Fatigue among patients with brain injuries has been linked to specific networks for attention in the brain, involving frontosubcortical regions.^43–45^ Möller and Nordin have shown that fatigue in mild traumatic brain injury is related to altered connectivity in the brain^45^ and that different neural networks are related to subjective compared with objective measures of fatigue.^31^ Whether similar patterns can also be seen in patients with pain and fatigue needs to be investigated. Connectivity changes have also been seen in CP, and patients with different pain conditions show connectivity changes.^46^ These studies have not included fatigue and fatigability and have not used task-fMRI in the scanner.

Since chronic low-grade inflammation is thought to play a major role in the onset of CP and some previous studies have shown elevated levels of inflammatory biomarkers in patients with chronic generalised pain and neuropathic pain,^47–50^ the immunological biomarkers in the present study are being investigated to improve knowledge on underlying mechanisms, which may lead to future potential diagnostic markers. A low-grade systemic inflammation may be related to fatigue and cognition as previous studies have suggested an upregulation or dysregulation of components in the immune system in patients with chronic fatigue syndrome,^51 52^ and Wåhlén *et al* have reported significant correlations between immunity proteins and psychological distress in patients with fibromyalgia.^53^ As an answer to the activation of the immune system activation in central immunocompetent cells such as microglia and astrocytes are initiated, resulting in a production of pro-inflammatory cytokines in the CNS that promotes a change in behaviour response characterised by decreased mood, increased anxiety, pain sensitivity, etc. Previous studies have investigated single inflammatory markers and reported inconsistent results.

There is, thus, a need for increased knowledge about the association between CP, cognition and fatigue and possible underlying pathophysiological mechanisms. To improve diagnostic and prognostic models, we aim to investigate the coexpression profile of inflammatory biomarkers and by applying network analysis we aim to discover cellular pathways that might be activated in cognitive fatigue.

### Objectives

The primary aim of the study is to investigate the presence of self-rated mental fatigue, objectively measured cognitive fatigability and executive functions and how these are related to other cognitive functions, pain-related factors, inflammatory biomarkers and brain connectivity in patients with CP.

Do patients with CP show more pronounced self-rated mental fatigue and cognitive fatigue compared with healthy controls?Are the different fatigue measures related to cognitive functions such as process speed and attention functions?What is the relationship between (a) cognitive impairments, as measured by several different cognitive tests, (b) mental fatigue as measured by Multidimensional fatigue inventory-20 (MFI-20) and visual scale on fatigue (VAS-f) or (c) cognitive fatigability as measured by Wechsler Adult Intelligence Scale-III (WAIS-III) Coding andthe duration of pain.generalisation or intensity of painand are they affected by covariates, such as sleep disorders and degree of depression/anxiety?Is there an association between immunological biomarkers and (a) cognitive functions, (b) mental fatigue and (c) cognitive fatigability?Does the connectivity in the brain of female patients with CP differ from healthy controls at rest as well as during activity while performing a vigilance task?Is there an association between connectivity in the brain andimmunological biomarkers.fatigability.results on neuropsychological tests?

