### Data analysis

For all study questions, descriptive statistics will be used to depict demographics, injury characteristics, results on neuropsychological tests and psychological screening instruments. Multiple linear and logistic regression will be used to detect any interaction effects. Parametric methods such as independent t test, one-sample t test (comparing with standardised test norms), Pearson correlation and multiple linear regression) will be used when data are normally distributed and non-parametric methods (Man-Whitney U-test, Spearman correlation, χ^2^, logistic regression) when data are skewed or on interval level or lower. Missing data will be listed as data loss. The significance level will be set to <0.05 (two-tailed).

Concerning study question 4, data from omics and targeted analysis will be analysed using advanced MVDA using SIMCA-P+. This is the recommended method in omics since it accounts for multicollinearity problems and missing data when the number of variables exceeds the number of observations.^72^ MVDA will be used for the analysis of the biomarkers. Principal component analysis (PCA), orthogonal partial least squares- discriminant analysis (OPLS-DA) and OPLS regression will be applied for analysis of the biomarkers and their ability to differentiate between groups and their correlation with clinical characteristics and outcomes. PCA is an unsupervised analysis that reduces the dimensionality of data and extracts and displays systematic variation in the data matrix. Outliers will be identified using score plots in combination with Hotelling’s T2 test (the distance from the origin in the model plane for each selected observation) and DModX (the distance of the observation to the X model plane). The values that are larger than the 95% confidence limit are considered suspicious and the values larger than the 99% limit should be considered strong outliers.^73^

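### The control for mood and sleep promised in the abstract is not carried into the question 4 biomarker analysis, so a marker related to mood can be flagged as a marker of self-rated mental fatigue

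*Protocol article*

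**What the plan says.** The abstract, directly after an aim that lists inflammatory biomarkers, states: "We will control for pain-related factors such as pain intensity and secondary factors such as sleep disturbances and psychological well-being".

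Under Objectives, question 3 asks of its relationships "are they affected by covariates, such as sleep disorders and degree of depression/anxiety". Question 4, the next item, is "Is there an association between immunological biomarkers and (a) cognitive functions, (b) mental fatigue and (c) cognitive fatigability" and names no covariate.

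The Data analysis section gives question 4 its own method: "Concerning study question 4, data from omics and targeted analysis will be analysed using advanced MVDA using SIMCA-P"+. The tools are principal component analysis, OPLS-DA and OPLS regression, used for group separation and for "their correlation with clinical characteristics and outcomes". Four criteria follow:
- a variable influence on projection (VIP) above 1.0;
- an absolute p(corr) above 0.4–0.5;
- CV-ANOVA below 0.05;
- a gap between R2 and Q2 of no more than 0.2–0.3.

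No adjusted, partial or stratified step appears. The purpose stated for regression is another one: "Multiple linear and logistic regression will be used to detect any interaction effects".

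The Introduction gives two links. On fatigue: "Correlations between depression and self-rated fatigue are seen in several studies regardless of the underlying medical condition". On biomarkers, a cited study "reported significant correlations between immunity proteins and psychological distress in patients with fibromyalgia". The Hospital Anxiety and Depression Scale (HADS) and the Insomnia Severity Index are among the register questionnaires.

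**The concern.** On the protocol's own evidence, distress is related both to the predictor (immunity proteins) and to one outcome of question 4 (self-rated fatigue). OPLS does not deal with this. It sets aside marker variation that is unrelated to the outcome, but variation shared with depression is related to self-rated fatigue, so it stays in the predictive component.

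The stake is interpretation. Inflammatory markers are a primary outcome in Table 1. The Introduction hopes for diagnostic markers and calls it important to capture fatigue without the result being affected by depression. If a marker of low mood is reported as a marker of mental fatigue, that purpose is missed and the reader has no adjusted result to set beside it.

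**Working it through.** **1. The plan's own figure.** The only calculated sample size is 24 per group for the Coding test (difference 2.5, SD 3.0, two-sided 5%, power 80%). Normal approximation: 2 × (1.960 + 0.842)² × (3.0/2.5)² = 22.6, so 23. The t-test version gives 23.6, so 24. It reproduces, and this point does not affect it. No calculation is given for question 4.

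**2. Inputs for question 4.** From the protocol: 36 blood-sampled patients, up to 92 targeted markers, and the flagging rule VIP > 1 with absolute p(corr) > 0.4 (lower end of the stated range). Assumed, because the protocol gives no coefficients: marker–depression correlation 0.3–0.5 and depression–fatigue correlation 0.4–0.7.

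**3. Induced correlation.** If a marker is tied to fatigue only through depression:

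r(marker, fatigue) = r(marker, depression) × r(depression, fatigue)

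This runs from 0.3 × 0.4 = 0.12 to 0.5 × 0.7 = 0.35. The chance of p < 0.05 for a single correlation with n = 36 uses z = arctanh(r) × √33. For r = 0.5 × 0.6 = 0.30, z = 0.3095 × 5.745 = 1.78, and the probability is 1 − Φ(1.96 − 1.78) ≈ 43%. Over the whole assumed range it is 11%–56%. This shows the mechanism only, since single-marker tests are not the planned method.

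**4. The planned flagging rule.** OPLS was simulated with one predictive and one orthogonal component, n = 36, 92 markers (10 tied only to depression) and 2,000 runs:

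| Marker–depression, depression–fatigue | Mood-only markers flagged | After removing depression | Unrelated markers |
|---|---|---|---|
| 0.3, 0.6 | 11% | 2.5% | 2.5% |
| 0.4, 0.6 | 18% | 2.7% | 2.5% |
| 0.5, 0.6 | 29% | 2.7% | 2.7% |
| 0.5, 0.7 | 41% | 2.6% | 2.6% |

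Mood-only markers are flagged about 4 (10.6/2.5) to 16 (40.7/2.6) times as often as unrelated ones. Removing depression takes the excess away.

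**5. Adding the model-level criteria.** A second simulation used the same layout with 7-fold cross-validation and 1,000 runs:

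| Marker–depression, depression–fatigue | VIP and p(corr) | + CV-ANOVA < 0.05 | + R2−Q2 < 0.3 |
|---|---|---|---|
| 0.3, 0.5 | 8% | 0.2% | 0% |
| 0.4, 0.6 | 18% | 1.9% | 0% |
| 0.5, 0.6 | 28% | 4.0% | 0% |

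A third simulation, again with 36 patients, 92 markers and assumed correlations, gave about 8%–44%, 0.2%–27% and 0%–1.3% for the three columns. In it, the R2−Q2 limit also removed every true signal when only 10 markers were truly linked to fatigue. That criterion guards against overfitting and does not distinguish a mood marker from a fatigue marker.

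**The case against.** The strongest reply is that control is stated. The abstract promises it for the study as a whole, the listed characteristics to which markers are related may include the depression and insomnia scales, and multiple linear regression appears among the general methods for all questions. A condensed article may leave the mechanics to a fuller plan. This stands against any reading that mood and sleep have no role in question 4, which a reader might infer and the documents do not support. It does not remove the mismatch. The article describes the question 4 analysis down to outlier limits, and none of that delivers the promised control. Using a depression scale as a separate OPLS outcome is not adjustment.

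A reader might take the 11%–56% in step 3 as the error rate of the planned analysis. It is not, because the plan has further criteria that cut the rate sharply.

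The protocol also describes immune activation as lowering mood. Mood may then be a mediator and the unadjusted association real, so a rule that only adjusted associations count as fatigue markers is not supported. This stands.

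Scope is limited too. For fatigability, the Introduction cites brain-injury studies in which depression had no effect. No link between sleep and biomarkers is stated, and the distress–protein link comes from fibromyalgia. The study calls itself explorative. All of this stands and narrows the point to part (b).

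**Conclusion.** The point holds in limited form. The abstract's promise, the covariates named for question 3 alone and the unadjusted method for question 4 do not fit together. On the protocol's own evidence the gap matters for self-rated mental fatigue.

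The size rests on assumed correlations, independent background markers and an assumed share of mood-related markers (10 of 92). Under the VIP and p(corr) rule, mood-only markers are flagged roughly 8%–44% of the time across the simulations. With CV-ANOVA added, the figure is about 0.2%–27%, and with the R2−Q2 limit about 0%–1.3%. The reduction comes from rejecting whole models, so a model that passes still cannot tell mood from fatigue.

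The harm is to interpretation, not to a confirmatory error rate. For sleep, the case rests on the abstract's promise and on the Introduction's remark that sleep disturbance interferes with fatigue questionnaires.

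**What to change.** State in the Data analysis section how the abstract's control applies to question 4(b). In the 36 blood-sampled patients:

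- Keep OPLS regression as the screen.
- Refit the selected markers, or the predictive score, against mental fatigue in a linear model with HADS depression as a covariate. Add the Insomnia Severity Index to honour the abstract.
- Report unadjusted and adjusted associations side by side. Describe those that disappear on adjustment as shared with mood or sleep, and say that cross-sectional data cannot separate confounding from mediation. Do not make adjustment a pass/fail rule.
- Treat adjustment of fatigability as optional.

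Selection and refit use the same patients, so the change in the estimate is more informative than the refit p-value. The analysis is best confined to patients, because the scales come from a patient register and the article does not say whether controls complete them.

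The cost is a few lines of wording, one extra table and slightly wider intervals. For one marker, two covariates take the residual degrees of freedom from 36 − 2 = 34 to 36 − 4 = 32. The data are already collected, and the article states that no analyses have been completed and reported, so the step can still be fixed in advance.

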## Methods and analysis

### Study design

This is a cross-sectional explorative case–control study. Strengthening the Reporting of Observational Studies in Epidemiology-reporting guidelines will be used.^54^

### Study setting

The Unit of Pain Rehabilitation at the Department of Rehabilitation Medicine at Danderyd University Hospital, Stockholm and the Department of Pain Rehabilitation, Pain Center, Umeå University Hospital, Umeå from September 2018 to October 2022. Data collection is now complete, but no analyses have been completed and reported.

### Participants

#### Patients for neuropsychological assessment

Two hundred outpatients between 18 and 50 years with CP from the Unit of Pain Rehabilitation at the Department of Rehabilitation Medicine at Danderyd University Hospital or from the Department of Pain Rehabilitation, Pain Center at Umeå University Hospital will be included. There will be no stratification of age, but the majority of the patients will be women as they are over-represented among those receiving rehabilitation for CP. In the analyses, the patients are compared with 36 healthy controls.

Please see the flowchart for an overview of the study (figure 1).

